
**Fig. 2 Fig2:**
[figure not shown]
GARDIAN-guided classification of risk and follow-up plan over 24 months

### Control group - standard care

Participants allocated to the standard care arm of MODERN received screening assessments but diluted risk factor management which was limited to receiving a brief risk assessment report and Health Passport with less intensive CVD and T2DM education and dietary and lifestyle advice. Ideal risk factor targets were identical yet care plans were not developed. GARDIAN status was not used to direct management and follow-up contacts at set times; aside from baseline, 12 month (mid), and 24 month (end) study visits, all management and follow-up was at the discretion of their usual health care providers. As per intervention group participants, control group participants were permitted to seek any relevant concomitant care.

### Follow-up visit format

For all participants randomized into a study group, self-report questionnaires posted 1 week prior to their scheduled visit collected updated information regarding health behaviours and general health at 12 and 24 month visits. Screening assessments, biochemistry, actigraphy and arterial stiffness tests were also repeated at 12 and 24 month visits for all participants. For intervention participants only, just screening assessments were conducted at all other (GARDIAN directed) clinic visits to help assess participant’s progress in achieving their health goals. Extended surveillance to 5 years post randomization of cardio-metabolic health and associated health care activity to determine the longer-term impact of the MODERN intervention is planned.

### Study power

A 15% difference (20% intervention, 5% control) in the number of subjects who achieved target risk factor thresholds or clinically significant changes in any 3 MetS risk factors was derived from sub-group analyses (of individuals identified with MetS) from a pilot intervention study [18] and a randomized controlled trial of a similar lifestyle intervention delivered by health professionals versus standard care [12]. With two-sided α = 0.05, an estimated minimum of 125 participants per study arm would provide 95% power to detect a 0.15 difference in the primary endpoint after 2 year follow-up. Accounting for potential loss-to-follow up of 15%, overall the trial would require approximately 150 participants randomized in each group.

### Data management, confidentiality and dissemination

Information collected under unique study identification will be returned to an independent data management unit for double data entry, range checks for data values, data queries to be resolved by data lock and coding according to standard operating procedures. Storage of paper documents will be filed in a locked compactus controlled by proxy access to authorised personnel. Electronic files will be saved in a secure server storage system that is accessible by authorised personnel in accord with information technology security processes. Data sharing and use by organisations involved in the study is guaranteed by clinical trial research agreements between collaborating institutions. Upon study completion, participants will receive a summary of group results and study findings will be presented in publications and presentations.

### Statistical analyses

All analyses will be performed according to a statistical analysis plan and on an intention-to-treat basis. Tests will be two-sided at the nominal level α = 0.05. Data from each clinic will be pooled and summarised. Descriptive statistics will summarise the socio-demographic, clinical and overall health profile of the sample at baseline and 24 months follow-up; discrete variables will be assessed by frequencies and percentages and group differences tested using χ^2^ tests with calculation of odds ratios and 95% CI, whereas continuous variables will be assessed using mean (SD) or median (IQR) and group differences compared using independent t-tests or Mann-Whitney tests for variables with skewed distributions. For dichotomous variables, multiple logistic regression using 24 month results as dependent variables will evaluate the independent correlates of achieving the primary and secondary endpoints, after adjusting for baseline results and socio-demographic characteristics. For continuous variables, mixed-model ANOVA will be performed to asses within (pre-post) and between-group (control-intervention) differences over time and multiple linear regression used to evaluate important predictors of response.

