**Methods:**

MODERN is a multi-centre, open, parallel group randomized controlled trial in regional Victoria, Australia. Participants were self-selected and individuals aged 40 to 70 years with MetS who had no evidence of CVD or other chronic disease were recruited. Those attending a screening visit with any 3 or more risk factors of central obesity, dyslipidemia (high triglycerides or low high density lipoprotein cholesterol) elevated blood pressure and dysglycemia were randomized to either nurse-led health and lifestyle modification (intervention) or standard care (control). The intervention included risk factor management, health education, care planning and scheduled follow-up commensurate with level of risk. The primary cardio-metabolic end-point was achievement of risk factor thresholds to eliminate MetS or minimal clinically meaningful changes for at least 3 risk factors that characterise MetS over 2 year follow-up. Pre-specified secondary endpoints to evaluate between group variations in cardio-metabolic risk, general health and lifestyle behaviours and new onset CVD and type 2 diabetes will be evaluated. Key outcomes will be measured at baseline, 12 and 24 months via questionnaires, physical examinations, pathology and other diagnostic tests. Health economic analyses will be undertaken to establish the cost-effectiveness of the intervention.

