### Selection criteria

Participants residing in, or in surrounding regions of Shepparton or Colac and aged between 40 and 70 years with any three or more risk factors for MetS [1] as shown in Table 1 at the time of screening were eligible. The equivalent HbA_1C_ level for increased risk of diabetes was used as a substitute for fasting plasma glucose [17]. Participants were included if they were capable of attending scheduled study clinic visits and able to provide informed consent. Participants outside the eligible age range with two or less identifiable risk factors, any diagnosed form of CVD, chronic kidney disease or other forms of chronic disease that resulted in the belief that participation would not be appropriate, were excluded. Participants were omitted from participating if they had neurological/cognitive impairment and/or were unable to provide written informed consent.

**Table 1 Tab1:** Criteria for metabolic syndrome classification [1]

Risk factor for MetS	Cut-point criteria
Elevated WC	Men: > 94 cm
	Women: > 80 cm
Elevated triglycerides	≥ 1.7 mmol/L
Reduced HDL-C	Men: < 1.03 mmol/L
	Women: < 1.29 mmol/L
Elevated BP	≥ 130/85 mmHg
Elevated HbA_1C_	≥ 5.7% (39 mmol/L)

*MetS* metabolic syndrome, *WC* waist circumference, *HDL-C* high-density lipoprotein cholesterol, *BP* blood pressure, *HbA*
_*1C*_ glycated haemoglobin

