### Secondary endpoints

Secondary endpoints included between group changes at 24 months in meeting the individual components of the primary endpoint (i.e. target thresholds and clinically significant changes); resolution of MetS status; incidence of T2DM, as indicated by initiation of glucose-lowering medication following confirmation of a diagnosis of T2DM or a HbA_1C_ level ≥ 6.5% [17]; incidence of CVD, defined by fatal events, a diagnosis of CVD or non-fatal CVD-related events requiring hospitalization; within and between group variations in health behaviours, general health and cardio-metabolic risk factors, and; health economic analyses of the utilisation and cost of pharmacological therapies, community health care, and cardio-metabolic specific medical interventions and hospitalizations to establish the cost-effectiveness of the MODERN intervention.

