### Procedures

A self-report questionnaire posted to participants in the week prior to their scheduled visit collected information regarding: *socio-demographic factors* including marital and work status, primary language spoken, income, education and ethnicity; *health behaviours* including smoking, diet and alcohol via the Dietary Questionnaire for Epidemiological Studies (DQES v2) [19], sleep and physical activity and sedentary behaviour via the International Physical Activity Questionnaire (IPAQ) [20] and; *general health* including history of CVD, associated conditions or other serious conditions, family history of CVD or diabetes, prescribed medications and adherence via the Medication Adherence Questionnaire (MAQ) [21], signs and symptoms of angina via the Rose Angina questionnaire [22], health related quality of life via the Assessment of Quality of Life – 8 Dimension (AQoL-8D) [23], perceived risk and health belief evaluation via item specific self-efficacy [24] and locus of control [25].

An on-line, discrete choice experiment during the week prior to their scheduled visit at baseline and at study end evaluated participant *preferences* for the attributes of a health and lifestyle management program they consider of greatest importance affecting their choice to participate in such programs.

The *screening assessments* were undertaken at a dedicated clinic or on-site at workplaces (for few organisations with large numbers of workers) by registered nurses according to a standardised protocol at baseline, prior to randomisation. The same registered nurse who conducted the screening assessment remained responsible for the follow-up assessments of each participant until study completion; due to standardising the management of participants and frequency of follow-up, a different nurse that managed participants from only one study group was not required to alleviate bias.

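### Continuous secondary outcomes are analysed without stated adjustment for the baseline value, which costs precision, and within-group change is part of an endpoint although it is open to regression to the mean.

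*Protocol article*

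**What the plan says.** The Statistical analyses section of the Protocol article gives three procedures for continuous outcomes.

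- In the sentence on descriptive statistics at baseline and 24 months: "group differences compared using independent t-tests or Mann-Whitney tests for variables with skewed distributions".
- As the model: "mixed-model ANOVA will be performed to asses within (pre-post) and between-group (control-intervention) differences over time".
- For explanatory purposes: "multiple linear regression used to evaluate important predictors of response".

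No covariate is named for any of them. For dichotomous outcomes the same paragraph plans logistic regression "after adjusting for baseline results and socio-demographic characteristics".

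The Secondary endpoints section includes "within and between group variations in health behaviours, general health and cardio-metabolic risk factors". Under Selection criteria, people "with any three or more risk factors for MetS [1] as shown in Table 1 at the time of screening were eligible". Under Procedures, the screening assessments were done "according to a standardised protocol at baseline, prior to randomisation", so the qualifying readings are also the baseline readings. The Randomisation section stratifies by presence of T2DM and blocks by clinic. The abstract states: "Key outcomes will be measured at baseline, 12 and 24 months".

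**The concern.** Two separate matters arise, and both concern continuous secondary outcomes only.

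**Precision.** The baseline value is collected for everyone, and for most risk factors it is probably the best predictor of the 24-month value. A pre-post ANOVA treats it as a second outcome, and a 24-month t-test ignores it. Using it as a covariate gives a smaller variance for the same randomised contrast and needs no further data. The article applies this principle to binary outcomes but does not state it for continuous ones.

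**Within-group inference.** Within-arm change is part of a pre-specified secondary endpoint, and the model has a pre-post term to test it. When people are enrolled because some readings were beyond a cut-point, those readings move back towards the mean on re-measurement. A within-arm p-value on such a factor can therefore look favourable in both arms when the programme does nothing. If it is reported beside the between-arm result, it invites misreading.

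**Working it through.** **The plan's own figure.** Study power gives 20% against 5%, two-sided α = 0.05, 95% power, 125 per arm, 15% loss and about 150 per arm randomised. With pooled variance and no continuity correction, and a mean proportion of 0.125:

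n = [1.960 × √(2 × 0.125 × 0.875) + 1.645 × √(0.20 × 0.80 + 0.05 × 0.95)]² / 0.15² = (0.917 + 0.749)² / 0.0225 ≈ 123.4, so 124 per arm.

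Power at 125 per arm is 0.952, and 125/0.85 = 147.1, so 148. The stated figures reproduce. They concern the binary primary endpoint; the article gives no power calculation for a continuous outcome.

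**Precision.** The correlation r between baseline and 24 months is not in the documents, so 0.5 to 0.8 is assumed, with equal variance at both visits. Relative to the 24-month comparison, the variance of the treatment contrast is:

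- 24-month t-test: 1
- group-by-time term of a two-visit mixed ANOVA (change score): 2(1 − r)
- ANCOVA: 1 − r²

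The variance ratios to ANCOVA are therefore 1/(1 − r²) for the t-test and 2/(1 + r) for group-by-time. The ANCOVA-equivalent size of 125 per arm is 125(1 − r²) and 125(1 + r)/2 respectively. Power is for an assumed effect of 0.25 SD with 125 per arm.

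| r | t-test / ANCOVA variance | group-by-time / ANCOVA variance | 125 per arm is worth: t-test | group-by-time | Power: t-test, group-by-time, ANCOVA |
|---|---|---|---|---|---|
| 0.5 | 1.33 | 1.33 | 94 | 94 | 51%, 51%, 63% |
| 0.6 | 1.56 | 1.25 | 80 | 100 | 51%, 60%, 70% |
| 0.7 | 1.96 | 1.18 | 64 | 106 | 51%, 72%, 79% |
| 0.8 | 2.78 | 1.11 | 45 | 112 | 51%, 88%, 91% |

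**Regression to the mean.** As an illustration, take one normally distributed factor on which all participants were selected above its population mean. The mean excess at baseline is φ(0)/[1 − Φ(0)] = 0.798 SD, and the expected fall with no treatment effect is 0.798(1 − r) SD. Null data were simulated 2,000 times per value of r with 125 per arm and tests at 5%.

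| r | Expected fall (SD) | Within-arm test significant |
|---|---|---|
| 0.5 | 0.40 | 99.7% |
| 0.6 | 0.32 | 98.6% |
| 0.7 | 0.24 | 94.7% |
| 0.8 | 0.16 | 81.9% |

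In the same runs the group-by-time test rejected in 5.1% to 5.8% and the 24-month t-test in 4.6% to 5.7%. The randomised comparison keeps its level; the within-arm test does not. Actual entry was on any three of five factors, so the fall on a given factor will differ from these values, most likely downwards, because some participants did not qualify on it.

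**The case against.** The strongest reply is that nothing here biases the trial's comparison. A repeated-measures group-by-time analysis is valid under randomisation, and against it the loss is modest: at r = 0.7, 125 per arm performs like 106. The t-test and Mann-Whitney clause sits in a descriptive sentence, so the larger ratios may not apply to the main analysis. A separate statistical analysis plan is mentioned and may add covariates. The linear regression might also carry baseline values, since its covariates are not listed. All of this stands, and it limits the size of the point. It does not remove it: the article names its methods for continuous outcomes, gives the regression a different purpose, and states baseline adjustment only for binary outcomes.

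A reader might infer more in four ways that the documents do not support.

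- *That regression to the mean would pass for a treatment effect.* It acts on both arms alike, and the aim and hypothesis are comparative. Nowhere does the article say that a within-arm change will count as evidence of benefit.
- *That the effect is diluted because a group main effect averages in the baseline visit.* That would halve the estimate, (0 + δ)/2, but the article never names this term as the treatment estimate. Differences over time most naturally means group-by-time.
- *That everyone was selected on every outcome.* Entry needed any three of five factors. Quality of life, physical activity, hs-CRP and arterial stiffness were not entry criteria.
- *That Mann-Whitney tests are wrong for skewed variables.* Transforming instead is a preference.

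**Conclusion.** The point holds in a limited form. As stated, the analysis of continuous secondary outcomes is valid but leaves precision unused: 11% to 33% extra variance for the group-by-time contrast, and 33% to 178% for a 24-month t-test if that were used for inference. These ranges rest on the assumed correlation of 0.5 to 0.8 and equal variances; the power figures also assume a 0.25 SD effect.

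Within-arm pre-post tests on the five entry factors are not interpretable as programme effects. The direction follows from the design. The false-positive rates of 82% to 99.7% belong to the simplified one-factor model and are not a forecast for this trial. The primary endpoint is binary, so neither its analysis nor its sample size changes.

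**What to change.** State in the analysis plan that, for each continuous outcome, the inferential comparison is the between-arm difference at 24 months with a 95% CI. Estimate it by ANCOVA, or by a mixed model of the 12- and 24-month values, with baseline value, clinic and T2DM stratum as covariates. Report within-arm change descriptively, without p-values, and word that secondary endpoint as a between-arm comparison. Keep the t-tests and Mann-Whitney tests, if at all, as descriptive support.

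The cost is wording and code. The baseline values and stratification factors are already collected, and no further participants or visits are needed.

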## Discussion

This study will be the first Australian-based trial to establish the evidence for the potential benefit of independent nurse-run clinics in the community and their cost-effectiveness in adults with common cardio-metabolic abnormalities. Findings will determine whether a nurse-implemented health and lifestyle modification program is more effective at improving MetS components and other major risk factors for the development of CVD and T2DM compared to standard care in adults who are in jeopardy the most by living away from urban areas where socioeconomic disadvantage is higher and specialist health care increasingly scarce [38, 39]. Importantly, our longer term study over 2-years with re-evaluation at 5 years of changes in health outcomes and health care utilisation will assess the enduring effect of nurse education and self-care and management coaching on CVD and T2DM prevention. Pending positive results and cost-effectiveness, we envisage more nurse-led clinics to be adopted outside of major cities and encompassing other chronic diseases as a key primary preventative initiative.

The novelty of the MODERN study will establish the feasibility of nurses to safely and effectively screen for the presence of MetS and deliver cardio-metabolic management based on a written protocol that integrates a systematic approach to individual assessment of risk and tailored management [16]. Nurse-led models of care provide the opportunity to maximise the use of finite resources and reserve health professional contacts for higher risk individuals. The response to the MODERN trial results however should not discount the role of general practitioners and specialists in managing chronic disease. In practical terms, MODERN will provide a model that improves the earlier detection and quality of preventative care through clear therapeutic targets for lifestyle change and risk factors, techniques to instigate behaviour change, schedules of follow-up visits and guidance to seek additional GP (or other health professional) input. With MetS driving the twin global epidemics of CVD and T2DM and the extent of the underlying burden imposed by MetS, the model being tested represents a pragmatic utilisation of the potential for nurses to manage cardio-metabolic disease and prevent or delay the development of CVD and/or T2DM.

The detailed health economic evaluation component of the MODERN trial has the distinct advantage to enhance the translation of research findings into sustainable improvements in routine clinical practice and patient outcomes. Supporting health economic analyses are lacking in the Australian context and evidence relating to the cost-effectiveness of nurse-led clinics remains an obstacle to overcome before next generation models of care can improve the quality of preventative health. At present, it is incontrovertible that components of the MetS cause risk for CVD and T2DM and the MetS is an ideal target for risk reduction programs, carried out by nurses with the competence and skill set that uphold cardio-metabolic disease prevention. The results of the MODERN trial will add to the evidence-base for the success or failure of a nurse-led health service delivery of care for combatting the likelihood of CVD and T2DM in individuals with the MetS.
